**PATIENT SELECTION CRITERIA**

Eligible patients must fulfill all inclusion criteria and none of the exclusion criteria.

**Inclusion Criteria:**

1. Adult patients aged 18 years or older;

2. Diagnosis of acute respiratory failure, defined by a ratio of the partial pressure of arterial oxygen to the fraction of inspired oxygen (PaO_2_/FiO_2_) less than 300 mmHg;

3. Clinical indication for bronchoscopy.

**Exclusion Criteria:**

1. Patients who are already intubated or have a tracheostomy in place at the time of screening.

2. Patients requiring immediate endotracheal intubation prior to bronchoscopy.

3. Patients with severe hypoxemia, defined as a PaO₂/FiO₂ ratio below 150 mmHg despite optimized supplemental oxygen therapy.

4. Patients with severe thrombocytopenia, defined as a platelet count less than 60 × 10^9^/L.

5. Patients with a recent acute myocardial infarction (within the preceding 6 weeks).

6. Patients with anatomical abnormalities or pathological conditions resulting in nasopharyngeal obstruction that preclude safe application of the nasal interface.

8. Patients with significant chest wall skin lesions or other contraindications that prevent the safe placement or accurate function of EIT monitoring.

9. Patients with known intolerance to HFNC oxygen therapy.

**STUDY DESIGN**

This study is a prospective, two-center, open-label, randomized controlled trial designed to evaluate the effectiveness and safety of modified HFNC oxygen therapy using a single-prong cannula interface compared with standard oxygen therapy (SOT) during bronchoscopy in patients with ARF.

The trial will be conducted in the ICUs of two tertiary hospitals and will enroll adult patients with acute respiratory failure who require diagnostic or therapeutic bronchoscopy. Eligibility will be assessed based on predefined inclusion and exclusion criteria, and written informed consent will be obtained from all participants or their legal representatives prior to enrollment.

Eligible patients will be randomly assigned in a 1:1 ratio to receive either modified HFNC oxygen therapy or SOT during the bronchoscopy procedure. Randomization will be stratified by study site to ensure balanced allocation across centers.

Due to the visible differences between the oxygen delivery devices, blinding of participants and treating clinicians is not feasible. To minimize potential assessment bias, outcome evaluation and statistical analysis will be performed by independent statistician blinded to treatment allocation.

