**OBJECTIVES**

**Primary Outcome**

To determine whether modified HFNC oxygen therapy, using a single-prong cannula interface, reduces the need for escalation of respiratory support within 24 hours after bronchoscopy in patients with ARF compared with standard oxygen therapy (SOT).

Escalation was defined as meeting any of the following criteria:

1. Requirement for invasive mechanical ventilation (IMV);

2. Requirement for non-invasive ventilation (NIV);

3. Requirement for HFNC oxygen therapy;

4. An increase in support parameters without changing the level of respiratory support: For NIV patients: a >20% increase in inspiratory positive airway pressure (IPAP), expiratory positive airway pressure (EPAP), or the fraction of inspired oxygen (FiO_2_); For HFNC oxygen therapy patients: a >20% increase in flow rate or FiO_2_; For low-flow nasal cannula oxygen therapy patients: a >50% increase in oxygen flow rate.

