**Step 6: Immediate post-procedure care**

Participants will continue on their allocated oxygen therapy during the recovery period. EIT measurements and arterial blood gas analysis will be performed at 2 hours after bronchoscopy. Patients will be closely monitored for respiratory deterioration or need for escalation of respiratory support.

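### The blinded statistician protects the analysis but not the ascertainment of the primary event, which is decided and recorded by people who know the arm

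*Protocol*

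**What the plan says.** Study Design describes an open-label trial and concedes that "blinding of participants and treating clinicians is not feasible". It then states its protection: "To minimize potential assessment bias, outcome evaluation and statistical analysis will be performed by independent statistician blinded to treatment allocation".

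The Primary Outcome section counts a patient as escalated if any of four criteria is met. The first three are a requirement for invasive ventilation, for NIV, or for HFNC ("Requirement for HFNC oxygen therapy"). The fourth is "An increase in support parameters without changing the level of respiratory support", with percentage rules for patients on NIV, HFNC or low-flow nasal cannula.

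Step 6 of Study Procedures keeps participants on the allocated device during recovery and adds: "Patients will be closely monitored for respiratory deterioration or need for escalation of respiratory support". Data Collection and Data Management have trained site staff and investigators complete the CRFs. Neither section says that they are blinded.

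**The concern.** A blinded evaluator protects an outcome when the evaluator makes the judgement, as with a scan or a laboratory value. Here the judgement is made earlier, when someone at the bedside starts a different form of support or raises a setting. Whoever evaluates the record later is reading a decision already taken with knowledge of the arm.

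If staff step up a patient on a reservoir mask more readily than a patient on HFNC, or the reverse, the difference enters the event count and looks like a treatment effect. No later masking removes it. The hierarchical secondary outcome is built on the same escalation and inherits the problem. A reader who takes the Study Design sentence at face value would rate the risk of bias in the primary comparison too low.

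**Working it through.** The protocol states no event rate, sample size or power, so there is no figure to reproduce. The check sets the sections side by side and adds simple arithmetic.

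**1. Where the event arises.** All four criteria (Primary Outcome) are support changes or a requirement for one. No section says what makes support required in the 24 hours after bronchoscopy, and Step 6 refers to need without defining it. Both arms share an SpO2 target above 90% (Interventions; Step 4), but it governs oxygen titration during preparation and the procedure. It is not stated as a criterion for later escalation. The protocol does not name who decides. That it is the treating team is an inference from Study Design and Step 6, though the natural one in an ICU.

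**2. What an evaluator must see.**
- Criterion 3: HFNC is also the experimental treatment and continues into recovery. If the record shows HFNC in use after the procedure, telling an event from the allocated treatment requires knowing the arm.
- Criterion 4: the rules are device-specific, so scoring needs device and settings. Starting settings are 60 L/min by HFNC at FiO2 0.8 in one arm and a reservoir mask at 10-15 L/min in the other (Interventions). Records from this period would usually show the allocation.
- If the statistician receives only a yes/no flag, blinding is preserved, but the site has already evaluated the outcome.

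On either route, blinded evaluation of the primary event is not secured as written.

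**3. Direction.** The reference level for an increase is not stated. If the study device were the reference:
- HFNC arm: FiO2 from 0.8 to 1.0 is (1.0 − 0.8)/0.8 = +25%, above the 20% HFNC threshold. Titration that the protocol allows could count as an event.
- SOT arm: mask flow from 10 to 15 L/min is (15 − 10)/10 = +50%. Criterion 4 has no rule for the mask, so this would not count.

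That works against HFNC. In the other direction, a patient on a mask can be stepped up to HFNC and meet criterion 3, while a patient already on HFNC cannot do so in the same way. The net direction cannot be read from the protocol.

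**4. Hypothetical size.** Assume a true need of 20% in both arms and discretionary step-ups in one arm only, adding 5 or 10 percentage points. None of these values comes from the protocol. Odds = p/(1 − p): 0.20 gives 0.250, 0.25 gives 0.333, 0.30 gives 0.429.

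| Extra step-ups in | HFNC | SOT | OR, HFNC vs SOT |
|---|---|---|---|
| SOT, +5 points | 20% | 25% | 0.250/0.333 = 0.75 |
| SOT, +10 points | 20% | 30% | 0.250/0.429 = 0.58 |
| HFNC, +5 points | 25% | 20% | 0.333/0.250 = 1.33 |
| HFNC, +10 points | 30% | 20% | 0.429/0.250 = 1.71 |

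The true odds ratio is 1 in every row.

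**The case against.** The strongest reply is that the sentence promises to minimise bias, not remove it, and that the same section openly says clinicians are unblinded. Much of the complaint is then about treatment decisions in an open-label trial, which are unavoidable, rather than about assessment. Criterion 4 has numeric thresholds that can be applied uniformly. Intubation and mortality among the other outcomes are less discretionary. Masked data handling and sensitivity analyses may be in the SAP, which is not at hand.

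Part of this stands, and it rules out three stronger readings.

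- A reader might infer that the safeguard is worthless. It is not: an independent analyst blind to arm still guards against biased coding and model choice.
- A reader might infer that the data always unblind the evaluator. The protocol does not say what the statistician receives. Criterion 4 names NIV and low-flow cannula, which are the study device in neither arm, and omits the mask. That fits a comparison with support before bronchoscopy, which is collected. On that reading some patients could be scored without seeing the procedural device. Unblinding is likely, not certain.
- A reader might infer that the trial is biased towards HFNC. Step 3 of the working shows why no direction can be claimed.

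The rest does not answer the point. The sentence claims outcome evaluation as well as analysis, and a SAP cannot undo a decision taken at the bedside. The numeric thresholds say how large a change counts, not when a change is warranted.

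**Conclusion.** The point holds in limited form. Blinding as described covers the statistical analysis. It does not cover ascertainment of the primary event, so the protocol claims more than it delivers. The conclusion rests on the absence of criteria for requirement, the unblinded status of clinicians, and the absence of any statement that recording staff are masked. It also assumes that the treating team decides escalation.

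No size can be given from the documents. The odds ratios of 0.75 to 0.58 show only that a modest difference in thresholds could produce an apparent benefit. This should be corrected. It does not invalidate the design, since open-label care is unavoidable here, but overstating the protection is avoidable.

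**What to change.** 1. Reword the Study Design sentence: blinding covers the statistical analysis, and escalation is decided and recorded by staff who know the arm.
2. State criteria for when support counts as required, and one reference support level for judging an increase, both identical in the two arms. Their content is for the clinical leads to set. The reference level must also be reconciled with the titration ranges under Interventions and with the missing rule for the mask.
3. At each step-up within 24 hours, record on the CRF the time, SpO2, respiratory rate, settings before and after, and the reason.
4. Keep all step-ups as the primary outcome. Add a prespecified sensitivity analysis limited to step-ups that meet the recorded criteria, reviewed with the arm masked where possible.

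Restricting the primary outcome itself to criteria-confirmed step-ups is not advised. It could drop real intubations that lack a recorded reason. Because the same unblinded staff complete the form, it would also exchange differential thresholds for differential documentation. The sensitivity analysis shares that second weakness and should be read accordingly.

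The cost is a few CRF fields, one extra analysis and a less favourable description of the blinding.

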**INTERVENTIONS**

**1. Modified HFNC oxygen therapy group**

Participants in this group will receive oxygen therapy via the AIRVO 2 system (Fisher & Paykel Healthcare, New Zealand) using a single-prong nasal cannula interface. The size of the nasal cannula was selected according to the patient’s nostrils to ensure proper fit and comfort. The system will deliver heated and humidified oxygen at an initial flow rate of 60 L/min and a fraction of inspired oxygen (FiO_2_) set at 0.8, titrated as needed up to 1.0 to maintain SpO_2_ above 90% during the procedure. All participants will remain on the assigned oxygen modality during the entire bronchoscopy procedure and for post-procedural observation until clinical stabilization.

**2. SOT group**

Participants in the control group will receive oxygen via a standard non-rebreathing reservoir mask with a flow rate of 10-15 L/min, titrated to maintain SpO_2_ above 90% during the procedure. The mask will remain in place throughout the bronchoscopy procedure. Oxygen therapy will continue until the patient is clinically stable following bronchoscopy.

**STUDY PROCEDURES**

The study will be conducted in a stepwise and standardized manner to ensure consistency across participating centers and to maintain patient safety. The key steps of the study procedures are outlined below:

**Step 1: Patient screening and enrollment**

Patients admitted to the ICU with AFR requiring bronchoscopy will be screened based on predefined inclusion and exclusion criteria. Eligible patients or their legal representatives will be approached for informed consent, with adequate explanation of study objectives, procedures, risks, and benefits.

**Step 2: Baseline assessment**

Collection of demographic data, medical history, and baseline clinical parameters, including vital signs, arterial blood gas analysis, and routine laboratory results.

**Step 3: Randomization**

Patients will be randomly allocated in a 1:1 ratio to either the modified HFNC group or the SOT group. Randomization will be stratified by study site using a computer-generated sequence and allocation will be concealed with sealed opaque envelopes.

**Step 4: Pre-bronchoscopy preparation**

The assigned oxygen delivery modality (modified HFNC or SOT) will be applied, titrated to maintain SpO_2_ >90%.

Continuous monitoring of vital signs and arterial blood gas analysis will be performed. A properly sized 16-electrode EIT belt will be placed around the patient’s chest, just below the axillae at the level of the fourth to fifth intercostal spaces. The belt position will be marked to prevent displacement during the study. The EIT belt will remain in place for continuous monitoring throughout the procedure.

Sedation will be provided using intravenous midazolam (0.05-0.1 mg/kg) and/or propofol (up to 1 mg/kg) based on patient needs. Topical anesthesia will be administered to the nasal and oropharyngeal mucosa.

**Step 5: Bronchoscopy procedure**

Bronchoscopy will be performed via nasal access following standard clinical practice. Diagnostic interventions such as bronchoalveolar lavage (BAL), bronchial brushing, endobronchial biopsy, or transbronchial lung biopsy will be performed when clinically indicated. Any procedural interruption or adverse events will be documented in real time. Vital signs and EIT parameters will be recorded at five predefined time points: T0, before bronchoscopy; T1, upon insertion of the bronchoscope into the nasal cavity; T2, at the end of the procedure; T3, 10 minutes after bronchoscopy; and T4, 2 hours after bronchoscopy.

**Step 6: Immediate post-procedure care**

Participants will continue on their allocated oxygen therapy during the recovery period. EIT measurements and arterial blood gas analysis will be performed at 2 hours after bronchoscopy. Patients will be closely monitored for respiratory deterioration or need for escalation of respiratory support.

**Step 7: Follow-up and outcome assessment**

Patients will be followed for up to 90 days to evaluate all primary and secondary outcomes, including short-term respiratory events and longer-term mortality.

**DATA COLLECTION**

Data will be collected prospectively using standardized case report forms (CRFs) specifically designed for this study. Trained research staff at each participating center will be responsible for accurate and timely data entry.

**1. Demographics and baseline characteristics**

(1) Age, sex, body mass index (BMI);

(2) Severity scores: APACHE II, SOFA;

(3) Smoking history;

(4) Comorbidities;

(5) Indication for bronchoscopy;

(6) Respiratory support prior to bronchoscopy;

(7) Baseline vital signs;

(8) Arterial blood gas analysis.

**2. Procedural data**

(1) Type of bronchoscopy and diagnostic interventions: BAL, bronchial brushing, endobronchial biopsy, transbronchial lung biopsy;

(2) Volume of BAL fluid instilled and recovered;

(3) Duration of bronchoscopy;

(4) Vital signs, including respiratory rate, heart rate, mean arterial pressure, and SpO_2_, as well as EIT measurements such as tidal impedance variation (TIV) and changes in end-expiratory lung impedance (ΔEELI), will be recorded at five predefined time points: T0, T1, T2, T3, and T4;

(5) Arterial blood gas analysis at T4.

**3. Intra-bronchoscopy and post-bronchoscopy events**

(1) Events during bronchoscopy: agitation, bronchospasm, arrhythmias/tachycardia ≥150 bpm, hypertension, epistaxis, mucosal bleeding;

(2) Events within 24 hours post-bronchoscopy: transient fever, pneumothorax, hemorrhage;

(3) Lowest SpO_2_ recorded during bronchoscopy;

(4) Number of procedure interruptions.

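### Named nasal, airway, cardiac and agitation events are recorded only during bronchoscopy, although the randomised oxygen device is worn before and after it

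*Protocol*

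**What the plan says.** The Study Design section makes safety an aim of the trial, which is "designed to evaluate the effectiveness and safety of modified HFNC oxygen therapy using a single-prong cannula interface". The harms to be collected are in Data Collection, section 3, as two lists divided by time:

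- "1) Events during bronchoscopy: agitation, bronchospasm, arrhythmias/tachycardia ≥150 bpm, hypertension, epistaxis, mucosal bleeding"
- "2) Events within 24 hours post-bronchoscopy: transient fever, pneumothorax, hemorrhage"

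The same section also collects the lowest SpO2 during bronchoscopy and the number of interruptions.

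Device exposure is described elsewhere. Step 4 applies the allocated oxygen before the scope is passed, in the same step as sedation. For the modified HFNC arm, the Interventions section says: "All participants will remain on the assigned oxygen modality during the entire bronchoscopy procedure and for post-procedural observation until clinical stabilization". For the control arm it says: "Oxygen therapy will continue until the patient is clinically stable following bronchoscopy". Step 6 repeats this for both arms: "Participants will continue on their allocated oxygen therapy during the recovery period".

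One general sentence on harms appears, in Step 5, the bronchoscopy procedure: "Any procedural interruption or adverse events will be documented in real time".

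**The concern.** The trial randomises an oxygen device, not a bronchoscope. The windows for most of the named harms follow the bronchoscope. If the lists are applied as written, a nosebleed, agitation, bronchospasm or arrhythmia that begins during recovery, with the allocated device still in place, has no listed field. The same holds for an event in Step 4, when the device is already on.

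The Trial Summary says that the investigators developed the single-prong interface themselves, and the Interventions section starts it at 60 L/min. How well it is tolerated over the whole time it is worn is therefore a central safety question. A statement that the interface is safe would rest mainly on the time when the scope was in place. The SAP cannot repair this, because it cannot analyse events that were never recorded.

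**Working it through.** The protocol gives no safety figure to reproduce, so the check is a comparison of sections.

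**Step 1. Match each named event to its window (Data Collection, section 3).**

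| Event | During bronchoscopy | 24 hours after |
|---|---|---|
| Agitation | yes | no |
| Bronchospasm | yes | no |
| Arrhythmia or tachycardia | yes | no |
| Hypertension | yes | no |
| Epistaxis | yes | no |
| Mucosal bleeding | yes | no |
| Transient fever | no | yes |
| Pneumothorax | no | yes |
| Hemorrhage | no | yes |

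Count: 6 during only + 3 after only + 0 in both = 9 terms.

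**Step 2. Set the windows against device exposure.** Exposure has three parts: preparation (Step 4), the procedure (Step 5) and recovery (Step 6, and the Interventions section for each arm). The six procedural terms are listed for the second part only. Recovery has no fixed length, since it ends at clinical stability.

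**Step 3. See what other recording routes cover after scope removal.**

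- *Vital signs.* Heart rate, mean arterial pressure, respiratory rate and SpO2 are recorded at T3 (10 minutes after) and T4 (2 hours after). A fast heart rate or high pressure at those moments would be seen. An arrhythmia between them, or agitation, bronchospasm or epistaxis at any time, would not.
- *Hemorrhage.* This is collected for 24 hours but not defined. It may or may not include a nosebleed or mucosal bleeding, so two sites could code the same event differently.
- *General adverse-event sentence.* It is not limited to the named list, but it stands in the procedure step. Step 6 asks for monitoring of respiratory deterioration and escalation only.
- *Primary outcome.* Bronchospasm severe enough to require more support within 24 hours would count as escalation, but not as bronchospasm. Milder events would leave no trace there.

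**Step 4. Ask whether the gap differs by arm.** Both arms have the same lists and windows, both keep the allocated device on afterwards, and bronchoscopy is nasal in both. Collection is therefore equal by arm. Harms that only the prong can cause are the exception: they arise in one arm, so those missed after scope removal are all missed in the modified HFNC arm.

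**Step 5. Look for an event that matches a risk the protocol names.** Known intolerance to HFNC is an exclusion criterion. Intolerance or early removal of the allocated device is on neither list.

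**The case against.** The strongest reply is that the lists summarise data items and nowhere say that other events are excluded. The case report forms are not shown and may hold more. Vital signs are monitored, bleeding is followed for 24 hours, and respiratory deterioration after the procedure is the primary outcome. On this view the point is a small form clarification.

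Part of that stands. The forms may go further than the protocol, and cardiac and bleeding data do not stop altogether when the scope leaves. But the protocol itself assigns each term to a window, and none of the other routes covers agitation, bronchospasm, epistaxis by name or an intermittent arrhythmia during recovery.

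The reply is right against several stronger readings that a reader might infer:

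- *That a pneumothorax during the procedure goes unrecorded.* It lacks a named field, but the general sentence in Step 5 covers one recognised at that time.
- *That desaturation below the 90% target is not captured.* The lowest SpO2 during bronchoscopy is collected, so a fall below 90% in the procedure can be derived. SpO2 is also recorded at all five time points.
- *That events are undercounted in the experimental arm only.* All six procedural events can occur in either arm, and the windows are identical.
- *That a stated share of device time is uncovered.* The protocol gives no procedure or recovery duration, so any percentage would rest on invented times. Time covered is also not the same as harm captured, because passing the scope through the nose can itself cause bleeding.

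**Conclusion.** The point holds in a limited form. Six of the nine named harms are tied to the time of bronchoscopy, although the randomised device is worn before it and for an open-ended period after it. The result is incomplete capture of device-period harms in both arms. For harms specific to the prong, the loss would favour modified HFNC. For the rest, the documents do not support a claim of bias between arms. The number of events missed cannot be estimated from the protocol.

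This rests on two assumptions: that the lists are applied as written, and that the case report forms add no later window for these events. The primary outcome is not affected. The weakness lies in the safety evaluation that the Study Design section promises, and it is worth correcting because the correction is small.

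**What to change.** In Data Collection, section 3:

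1. Replace the two time-divided lists with one list of the nine events, recorded in both arms over one fixed window: from application of the allocated oxygen (Step 4) to 24 hours after bronchoscopy.
2. Record onset time for each event, so that those during and after the procedure can still be reported separately.
3. State whether hemorrhage includes epistaxis and mucosal bleeding.
4. Add intolerance or early removal of the allocated device as an event in both arms.

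The end of the window should stay fixed and not be tied to device removal. Device time is open-ended and could differ by arm, which would make the windows unequal.

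The cost is a protocol amendment and one revised case report form page, filled from bedside monitoring and ICU charts. The downside is that more minor events will be reported, probably more of them in the modified HFNC arm. No treatment or clinical rule changes.
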